### Randomisation and blinding

Enrolled participants who meet the eligibility criteria will be randomised to one of two groups which will dictate the order in which they receive the LGI or HGI diet. They will then receive the second diet depending on which diet they have first received. The random allocation sequence (AB or BA) will be generated by one of the trial co-ordinators; who will have no contact with the participants, using block randomisation by impartial biostatistics. The online randomisation package (http://randomization.com) will be used to allocate the sequences of the diet groups to the participants in equal numbers. Once the random number is generated, both trial investigators and participants are aware of the diet sequence (ie, whether the participant is going to start with LGI diet; A or HGI diet; B). The diets then will be delivered to the participant according to the sequence. The trial outcome measures will be determined by blinded researcher using codes on samples that will be sent for 16S ribosomal RNA (rRNA), blood marker and MRI/CAP-FibroScan analyses. The blinded allocation will be provided to the study statistician at the end of the study and once the analysis has been completed, the study statistician will be provided with the unblinded allocation.

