Soft cheese	51	129	1.5	2.7	12.4	0	34	0.51
Meal total		745	99	23.2	28.4	12.5	35.32	34.96
Dinner								
Lasagne (ready meal)	290	413	42	21.5	17.7	4.9	36	15.12
Apple	174	92	20	1	0.87	2.1	38	7.6
Semi-skimmed milk	150	71	6.8	5.3	2.6	0	25	1.7
Fruit and nuts mix	60	267	24.6	8.4	15	3.9	15	3.69
Meal total		843	93	36.2	36.1	10.9	30.22	28.11
Menu total		1999 kcal	264 g (52.7%)	78 g (15.5%)	71 g (31.8%)	46 g	36.64	94.594

GI, Glycaemic Index; GL, glycaemic load; HGI, High Glycaemic Index; LGI, Low Glycaemic Index.

The GI values of commercial food items are generated from that reported by Henry *et al*,^47^ as well as Nutritics software databases (Nutritics). The dietary GI of the menu is calculated from GI proportional contribution to total carbohydrate using the equation: GI=∑(C_food_/C_total_) × GI_food_; where C_food_ is the amount of carbohydrate contained in each digested food (g), C_total_ is the total carbohydrate in the meal and is the reported GI of the food.^21^ The GL of the diet is calculated based on the dietary GI and the amount of carbohydrate provided (the same in both diets) using the following equation: GL=(GI_food_ × C_food_)/100; where GI is the GI of each digested food and food is the amount of carbohydrate in the food.^21^ Food composition analysis and evaluation were performed using Nutritics software (Nutritics, Dublin, Ireland, 2018).

Participants will be provided with the food at the start of each 2-week diet period and will be clearly instructed on safe food storage and reheating. They will be required to complete dietary compliance sheet on a daily basis. Instructions on dietary compliance will be given at each study period and the dietary compliance records will be reviewed regularly during the intervention to assess their compliance. For the first 1 week prior to the intervention (1-week standardisation), and during the 4-week wash-out period, participants will be asked to avoid eating probiotics, yoghurt and cultured milk drink; if any, to standardise their gut microbiota and avoid any carry-over effects as shown in previous studies.^48 49^ Meal-timing will be standardised among all participants as much as possible during the intervention as well as during the standardisation period.

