### Sample size calculation and justification

The sample size is calculated using nQuery based on previous completed study by Bawden *et al*.^21^ Based on their pilot data, baseline liver fat fractions of both diet groups were 2.4±1%–1.2%, and after 1 week were HGI (High GI)=4.7% ± 2% and LGI=1.6 ± 0.7%. Using a two-group t-test (cross-over analysis of variance (ANOVA)) between the post-diet values with a 0.05 two-sided significance level, this produces a sample size of n=8 in each diet sequence (a total sample size of 16). This sample size has an 80% power to detect a difference in means of 3.1 (the difference between a Treatment 1, µ_1_, of 4.7 and a Treatment 2, µ_2_, of 1.6) with the assumption that the crossover ANOVA sqrt (MSE) is 2.828 (the SD of differences, σ, is 4). Assuming that 40% of people would drop out from cross-over study design, it is expected that at least 24 participants would need to be recruited.

The effect from the pilot study by Bawden *et al* pilot study (n=7) was an average 1.6%±0.7% decrease in liver fat fraction after following a 1-week LGI diet (p<0.05). Given that baseline liver fat fraction was 2.4%, in order to see such change with 80% power (p<0.05) we have doubled the participant numbers to n=16 using nQuery software to detect statistically significant differences.^21^ Our group has recently completed a study (ClinicalTrials.gov Identifier: NCT03844165) in which 84 participants with NAFLD followed either an LGI food enriched diet or their normal diet. Patients who changed their diet were found to have a significant decrease in liver fat after 16 weeks (from 20.4% to 18.8%) and had a statistically significant decrease in fasting glucose levels after the diet compared with the control group patients following their normal diet. This provides strong support to our hypothesis and demonstrates that a simple dietary change can have measurable impact on NAFLD symptoms in a short period. In another previous randomised crossover trial, metabolic changes were seen within 2 weeks in a dietary intervention with 10 participants.^66^ Based on these different approaches, we conclude that a sample size of 16 at the end of the study is sufficient. Assuming a 33% drop-out rate we estimate that it will be necessary to enrol n=24 NAFLD participants to achieve n=16 completing the two diet-interventions. This dropout rate has been reported in other dietary interventional studies.^67^

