### Statistical analysis plan

Baseline characteristics of participants, outcome measures at baseline (liver fat content, blood biomarkers and gut microbial composition) at each period time point will be summarised by diet group using descriptive statistics. The differences between the two interventions (LGI and HGI diet) will be tested by matched-pair Student’s t-test. Two-way repeated measures ANOVA test will be used to evaluate the effects of diets and time sequences on liver fat content, as well as on gut microbial composition and blood biomarkers and/or interactions with liver fat content, gut microbial composition and blood biomarkers. Data will be presented as mean±SD and the significance of difference will be set at p<0.05. Any changes in the planned statistical methods will be documented in the trial report. Data input, cleaning and analysis will be conducted using Stata software package. All analyses will be conducted on University of Nottingham computers/laptops that are regularly backed up to University of Nottingham servers.

Microbiome analyses: OTUs with a relative abundance of <0.1% in every sample will be removed, and relative OTU abundances will be inverse normal transformed before further analysis. Associations between response to LGI diet and OTU abundance at genus level will be predicted using a general linear model adjusted for age, gender and BMI. OTUs will be assumed to be significantly associated with response to the dietary intervention with a value <0.05 after adjusting for false discovery rate.

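### The wash-out is justified for gut microbiota only, and the article does not say how the pre-diet liver-fat scans protect the primary LGI–HGI comparison against possible carry-over

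*Protocol article*

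**What the plan says.** All references are to the protocol article.

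- **Primary objective.** The effect of the LGI versus the HGI diet on liver fat after 2 weeks.
- **Study protocol.** Two 2-week diet periods are separated by a 4-week wash-out, with MRI before and after each period.
- **Design of the dietary interventions.** In the standardisation week and the wash-out, participants are asked to avoid probiotics, yoghurt and cultured milk drinks. The stated purpose is "to standardise their gut microbiota and avoid any carry-over effects as shown in previous studies". This is the only wash-out instruction in the text.
- **Randomisation and blinding.** Once allocation is generated, "both trial investigators and participants are aware of the diet sequence".
- **Sample size calculation and justification.** The calculation is made "Using a two-group t-test (cross-over analysis of variance (ANOVA)) between the post-diet values", "with a 0.05 two-sided significance level". It gives "n=8 in each diet sequence (a total sample size of 16" participants), and the text adds: "This sample size has an 80% power to detect a difference in means of 3.1". The assumption is that "the SD of differences, σ, is 4".
- **Statistical analysis plan.** Baseline outcome measures "at each period time point will be summarised by diet group using descriptive statistics". The two diets are then compared by a matched-pair t-test, without saying whether its input is the post-diet value or the change. A two-way repeated measures ANOVA on diets and time sequences is also named.

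**The concern.** The article does address carry-over, but with a measure aimed at a secondary outcome. Avoiding probiotic and cultured products does not control dietary glycaemic index, which is the exposure under test, and it says nothing about liver fat. In a 2×2 cross-over, any effect of the first diet that lasts into period 2 is added to the value recorded under the other diet. If it acts in the same direction as the original effect, it pulls a post-diet LGI–HGI contrast towards zero.

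The trial would then understate its primary effect, with little power in reserve. The scan taken before period 2 is the one measurement that could reveal and partly correct this. The text commits it only to a descriptive summary.

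**Working it through.** **1. Reproduce the planned sample size.** Inputs from the sample size section: difference 4.7 − 1.6 = 3.1, SD of differences 4, two-sided 0.05, N = 16.

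- sqrt(MSE) = 4/√2 = 2.828, as stated.
- Standard error = 4/√16 = 1.0; noncentrality = 3.1/1.0 = 3.1; df = 16 − 2 = 14.
- Noncentral t power = 82.2% with 8 per sequence and 75.9% with 7 per sequence.

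So 8 per sequence is the smallest number that reaches 80%, and the stated figure reproduces.

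**2. Effect of carry-over on a post-diet contrast.** Let a and b be the LGI and HGI effects. From the quoted pilot, a = 1.6 − 2.4 = −0.8 and b = 4.7 − 2.4 = +2.3, so a − b = −3.1. Let r be the fraction of the first diet's effect still present at the second post-diet scan. Leaving out period effects, which cancel with equal sequences, LGI minus HGI is:

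- LGI first: a − (b + ra)
- HGI first: (a + rb) − b
- Average: (a − b) + r(b − a)/2 = (a − b)(1 − r/2)

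The size of the contrast is therefore 3.1 × (1 − r/2). The documents give no r, so the values below are an assumed range and not an estimate.

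| r (assumed) | Contrast | Loss | Power, N = 16 | Completers for 80% |
|---|---|---|---|---|
| 0 | 3.10 | 0% | 82.2% | 16 |
| 0.10 | 2.95 | 5% | 78.2% | 18 |
| 0.25 | 2.71 | 12.5% | 71.3% | 20 |
| 0.50 | 2.33 | 25% | 58.1% | 26 |

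**3. What r would mean in time.** The second post-diet scan falls 4 + 2 = 6 weeks after diet 1 ends. Under assumed first-order decay with half-life h weeks, r = 2^(−6/h). For h = 1, 2 and 4:

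- r = 0.02, 0.13 and 0.35
- contrast = 3.08, 2.91 and 2.55
- power = 81.6%, 77.1% and 66.1%

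An r of 0.50 needs a 6-week half-life.

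**4. Would a plain change from the pre-diet scan do?** At the second pre-diet scan the remaining fraction is 2^(−4/h). The change-score contrast is 3.1 × [1 + (2^(−4/h) − 2^(−6/h))/2], which gives 3.17, 3.29 and 3.33 for the same half-lives. It errs the other way, so how the pre-diet scan enters the model matters.

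**5. Adjusting for the pre-diet difference.** I simulated 8 + 8 participants. The inputs are assumptions that do not come from the documents: SD of between-period drift 2 points, measurement SD 1, response SD 1.5.

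- With no carry-over, the adjustment lowered the standard error from about 0.81 to 0.73.
- With r = 0.25 held through period 2, the contrast was 2.94 adjusted against 2.71 unadjusted.
- With r = 0.50, it was 2.73 against 2.33.

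The adjusted values stay below 3.1, so the correction is partial. Without carry-over, the standard error falls by roughly the factor √(1 − ρ²), where ρ is the correlation between pre-diet and post-diet differences. For assumed ρ of 0.3 to 0.7 that is a reduction of 5% to 29%, before the small cost of one degree of freedom.

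**The case against.** The strongest reply is that a wash-out exists and may well be long enough. It is twice the length of a diet period, participants are off study food, and they were selected for a habitual glycaemic index of at least 60. In the healthy-volunteer pilot, liver fat moved within 1 week. This stands: a return of liver fat is possible. It is simply neither specified nor verified.

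The article's NAFLD figure (20.4% to 18.8% over 16 weeks) might be read as proof of slow reversal. It is not. It is a start and an end value on a different dietary intervention, and it says nothing about what happens after stopping. If change in NAFLD really is slow, the assumed 3.1-point effect after 2 weeks is itself doubtful.

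The table also assumes that both diets' effects persist equally. If only the LGI effect of −0.8 persisted, the bias would be 0.8r/2 = 0.4r. At r = 0.50 that leaves 3.1 − 0.2 = 2.9, a loss of about 6% and not 25%.

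It can fairly be said, too, that the post-diet contrast is stated only in the sample size section, that the repeated measures ANOVA may use the pre-diet scans, and that covariate detail is often left to a separate analysis plan. A reader therefore cannot infer that the pre-diet scans are certainly unused. Nor can a reader infer that no wash-out diet instruction or food record exists, because the schedule figure and the participants' home booklet are not shown. What remains is that the article names its tests, its sizing contrast and its carry-over measure, and none of these, as written, visibly protects the primary outcome.

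**Conclusion.** The point holds in a limited form. The stated wash-out rationale concerns microbiota, no liver-fat basis is given for 4 weeks, and the text does not say how pre-diet liver fat enters the primary comparison. Carry-over could bias a post-diet contrast towards zero. The documents do not show that it does.

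The size is conditional on r. The plan's reserve is thin, since an assumed r of 0.10 already takes power from 82% to 78%. The 25% loss and 58% power at r = 0.50 mark the upper end of the assumed range and require half of both diets' effects to last 6 weeks. The power figures rest on the plan's own difference of 3.1 and SD of differences of 4. The case for adjustment does not depend on carry-over, because precision improves wherever pre-diet and post-diet differences are correlated.

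**What to change.** 1. Name one primary analysis of MRS liver fat: a cross-over model with period, adjusted for each participant's pre-diet difference (period 1 minus period 2). In practice, regress the post-diet difference, period 1 minus period 2, on sequence and on the pre-diet difference. The diet effect is half the adjusted sequence difference. With 16 completers the residual df falls from 14 to 13.
2. Report the change in pre-diet liver fat from period 1 to period 2 by sequence, with a confidence interval, as the check on the wash-out. With 8 per sequence this is descriptive evidence and should not decide which analysis is used.
3. State that the adjustment only partly removes carry-over bias if carry-over exists.
4. Reconcile the wash-out text with the primary liver-fat objective: give the liver-fat basis for the wash-out length, or say that there is none and that item 2 is the safeguard. What participants eat during the wash-out is for the investigators to decide and is not proposed here.

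Items 1 to 3 use scans already planned and cost one degree of freedom and a few lines of text. Item 4 costs a sentence or two.

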### Data collection and analyses of outcome measures

The timing and frequency of study measurements are depicted in figure 1. Participants will be asked to come fasted (a minimum of 8 hours) for each laboratory visit (pre and post each intervention period) and the following measurements will be made:

Anthropometric measurements: Participant height (cm), weight (kg), waist circumference (cm), body mass index (BMI) (kg/m^2^) and body composition with bladder voided using bioelectrical impedance analysis Analisi Composizione Corporea (BIA-ACC) appliance model BIA00A; (BioTekna, Marcon VE, Italy).Liver fat assessment: Hepatic fat fraction and comparison lipid composition will be measured using a Philips 3T Acheiva MRI scanner with 32 channel receive XL torso coil and advanced lipid composition analysis on a Philips 7T Acheiva scanner with eight channel multitransmit body coil. MRS will be acquired from a 20×20×20 mm voxel within the lower right lobe of the liver using Stimulated Echo Acquisition Mode localisation to assess hepatic fat fraction and composition. Spectra will be acquired over four echo times (20, 30, 40, 80) to correct for T_2_ relaxation over five breath-holds. Water will be used as a reference peak, and water suppression used to analyse signal from lipids. Spectra will be post processed (phase corrected, line-broadened, frequency aligned and averaged) as described previously,^50^ and then fitted according to known lipid signal positions.^51^ T_2_ corrected PDFF will be calculated as PDFF=FAT/(FAT +WATER) and converted to true mass fat fraction using known tissue values.^52^ Lipid composition will be estimated using individual peak amplitudes.^53^ Subcutaneous and visceral fat volumes will be determined using gradient echo MRI.^54^

Liver fat levels will also be assessed with the CAP scored using FibroScan, which has previously been evaluated against MRS^55^ as well as liver biopsy^56^ in cross-sectional cohorts. Although MRI-PDFF more accurately classifies steatosis,^57^ portability, accessibility and costs favour CAP associated with transient elastography. However, CAP has not been evaluated as a marker of efficacy of intervention. For the purpose of validation, participants will undergo a CAP-FibroScan at each intervention visit to quantify their liver fat levels.

Hepatic ATP flux: Rate of mitochondrial ATP turnover in the liver will be assessed using a Philips 3T MRI scanner with a Philips Phosphorous (31P) single loop surface coil. 31P MRS will be acquired from the liver using a 60 mm thick slice to avoid contamination from abdominal muscle. A progressive saturation scan protocol (five spectra acquired with varying length presaturation pulses) will be used to determine apparent T1.^58^ Two 31P MR spectra will then be acquired with full saturation of gamma ATP (−2.5ppm) and mirrored downfield of the inorganic phosphate peak (~14 ppm) respectively. An in-house fitting programme will be used for postprocessing spectra and measuring the saturation transfer to the inorganic phosphate peak and used to determine hepatic ATP flux rate constant. ATP concentration will also be determined from spectra and used to calculate final ATP flux rate values.^59^
Metabolic Biomarkers: Blood samples (not more than 80 mL at each visit) will be taken from fasted participants (12-hours fast) for analyses of metabolic analytes such as: glycaemic, insulinaemic, liver, lipid, haematological profiles, gut hormones (ghrelin, leptin, glucagon-like peptide-1 (GLP-1), glucagon) and plasma SCFAs. Although GLP-1 levels increase in response to meal ingestion, levels can be directly affected by presence of SCFAs, produced from fermentation of certain carbohydrates which may have been recently consumed, confounding the results. Instead, only fasting levels will be measured as short-term diets containing different carbohydrates types and different GI content have been found to affect fasting GLP-1 levels.^60^ In addition, circulating plasma SCFAs levels will be measured as it has been shown to be strongly related to metabolic health.^61^ Measurement of plasma SCFAs levels also overcomes the challenges associated with accurate quantification of volatile SCFAs molecules in faecal samples.^62^

All biochemical parameters concentrations will be assessed by a central laboratory that uses standard methods. Standard operating procedures will be followed for all laboratory assays to ensure the high quality and reliability of our generated data. Routine blood tests will be analysed by the accredited laboratories. Samples will be stored in −80 °C freezers until the study ends, under yearly service contract and monitoring systems. Analyses will be done according to assay manufacturer advice and completed by technicians and research staff who are formally trained or outsourced to collaborators or external suppliers where necessary. The insulin resistance will be estimated using homeostatic model assessment of insulin resistance (HOMA-IR). HOMA-IR is calculated according to the equation (HOMA-IR = (FPI×FPG)/22.5); where FPI is fasting plasma insulin, and FPG is fasting plasma glucose.^4^

Gut Microbiota Composition: Each participant will be asked to collect fresh stool sample in a standard laboratory container and bring it to the research centre with an ice pack for storage at −80°C. Stool samples will be processed using a standard commercial kit for (DNA)extraction.^63^ Then, the gut microbiota composition will be assessed using 16S sequencing of rRNA. DNA will be diluted to 20 ng/µL for 16S rRNA amplification and sequencing. Water negative controls will be included from extraction, through PCR to sequencing and select samples were sequenced in duplicate for quality control. The V4 region of the 16S rRNA gene will be amplified using universal primers 355F (CCAGACTCCTACGGGAGGCAGC) and 806R (GGACTACHVGGGTWTCTAAT). Amplified DNA will be sequenced on the MiSeq platform (Illumina). Read filtering and clustering will carried out using the MYcrobiota pipeline. Briefly, chimeric sequences will be filtered using the VSEARCH algorithm within Mothur, and reads will be clustered into operational taxonomic units (OTUs) using closed-reference clustering against the SILVA database v132 based on a 97% similarity. Diversity metrics (Shannon index, observed OTUs and Unweighted UniFrac) will be calculated by rarefying the OTU table down to 7000 sequences per sample 50 times and taking the average. These analyses will be carried out in QIIME V.2 (V.2018.11).^64 65^
Subjective Sensation Assessments: VAS scores will be used to assess the participant’s subjective appetite (hunger and fullness) during the intervention. Participants will be provided with a booklet to record their subjective appetite before and after each meal during the intervention at selected days.

### Sample size calculation and justification

The sample size is calculated using nQuery based on previous completed study by Bawden *et al*.^21^ Based on their pilot data, baseline liver fat fractions of both diet groups were 2.4±1%–1.2%, and after 1 week were HGI (High GI)=4.7% ± 2% and LGI=1.6 ± 0.7%. Using a two-group t-test (cross-over analysis of variance (ANOVA)) between the post-diet values with a 0.05 two-sided significance level, this produces a sample size of n=8 in each diet sequence (a total sample size of 16). This sample size has an 80% power to detect a difference in means of 3.1 (the difference between a Treatment 1, µ_1_, of 4.7 and a Treatment 2, µ_2_, of 1.6) with the assumption that the crossover ANOVA sqrt (MSE) is 2.828 (the SD of differences, σ, is 4). Assuming that 40% of people would drop out from cross-over study design, it is expected that at least 24 participants would need to be recruited.

The effect from the pilot study by Bawden *et al* pilot study (n=7) was an average 1.6%±0.7% decrease in liver fat fraction after following a 1-week LGI diet (p<0.05). Given that baseline liver fat fraction was 2.4%, in order to see such change with 80% power (p<0.05) we have doubled the participant numbers to n=16 using nQuery software to detect statistically significant differences.^21^ Our group has recently completed a study (ClinicalTrials.gov Identifier: NCT03844165) in which 84 participants with NAFLD followed either an LGI food enriched diet or their normal diet. Patients who changed their diet were found to have a significant decrease in liver fat after 16 weeks (from 20.4% to 18.8%) and had a statistically significant decrease in fasting glucose levels after the diet compared with the control group patients following their normal diet. This provides strong support to our hypothesis and demonstrates that a simple dietary change can have measurable impact on NAFLD symptoms in a short period. In another previous randomised crossover trial, metabolic changes were seen within 2 weeks in a dietary intervention with 10 participants.^66^ Based on these different approaches, we conclude that a sample size of 16 at the end of the study is sufficient. Assuming a 33% drop-out rate we estimate that it will be necessary to enrol n=24 NAFLD participants to achieve n=16 completing the two diet-interventions. This dropout rate has been reported in other dietary interventional studies.^67^

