Box 1Eligibility criteriaInclusion criteriaAdult males and females aged from 18 to 65 years (balanced number).Detected non-alcoholic fatty liver diseases (NAFLD) by controlled attenuation parameter (CAP)-FibroScan >288 dB/m or by MRI-proton density fat fraction >5% fat of liver weight.Body mass index ≥25 kg/m^2^.Abdominal obesity (waist circumference >102 cm for males and >88 cm for females).Have current moderate to high Glycaemic Index diet intake of ≥60 (Assessed from a completed 7-day day food diary).Available to give informed consent.Available to undergo MRI/spectroscopy and CAP-FibroScan.Exclusion criteriaCurrent smokers and excessive alcohol drinkers (>14 units/week).Perimenopausal (irregular periods) women.Participants with other liver abnormalities.Participants with history of gastrointestinal surgeries, depression, eating disorders or difficulties.Participants using pharmacological agents for obesity or NAFLD.Participants with type 1 diabetes.Participants with type 2 diabetes on second line medications (eg, glucagon-like peptide-1 analogues).Participation in any other trial in the last 3 months.Participants on any special diets (eg, vegetarians).Intolerance to foods included in the diet plan.

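### The 80% power at 16 completers holds only for a 3.1-point contrast taken from healthy volunteers; the same section also claims it for a 1.6% decrease, where its own SD gives about 32%

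*Protocol article*

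**What the plan says.** All of this is in the protocol article under Sample size calculation and justification, unless another place is named.

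- **First paragraph.** The planning values come from a pilot in which liver fat was about 2.4% at baseline and "after 1 week were HGI (High GI)=4.7% ± 2% and LGI=1.6 ± 0.7"%. The test compares the diets "between the post-diet values with a 0.05 two-sided significance level", and "this produces a sample size of n=8 in each diet sequence (a total sample size of 16"). The power statement is "This sample size has an 80% power to detect a difference in means of 3.1", with the root mean square error of the cross-over ANOVA assumed to be 2.828, equivalent to an SD of differences of 4.
- **Second paragraph.** It describes the effect in the pilot (n=7) as an average decrease of 1.6% ± 0.7% on the LGI diet, and says that 16 participants give 80% power to see that change from a baseline of 2.4%. It then cites the group's own study of 84 patients with non-alcoholic fatty liver disease (NAFLD): "Patients who changed their diet were found to have a significant decrease in liver fat after 16 weeks (from 20.4% to 18.8"%). The comparator there was normal diet. After mentioning one further small cross-over trial, it ends: "we conclude that a sample size of 16 at the end of the study is sufficient".
- **Population.** The abstract and the discussion describe the pilot participants as healthy volunteers. This trial enrols NAFLD patients, identified by a FibroScan score or by "MRI-proton density fat fraction >5% fat of liver weight" (Box 1).
- **Duration.** Each diet lasts 2 weeks.

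**The concern.** The section makes a firm claim of sufficiency for the primary outcome. It rests on one effect size from people whose mean liver fat was below this trial's MRI threshold for disease. The second paragraph then attaches the same 80% to a change about half as large, without a second calculation and without stating another SD. For a fixed sample size and SD, power rises with the difference, so 16 participants cannot have 80% power both for 3.1 and for 1.6 points.

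What is at stake is how the result will be read. A reader who accepts the section will believe that the trial had 80% power for a change of 1.6 points. A non-significant result could then be taken as evidence that glycaemic index does not matter in NAFLD, when differences of that size would remain compatible with the data.

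**Working it through.** **Inputs.** N = 16 completers (8 per sequence), two-sided alpha 0.05, SD of differences 4, differences of 3.1 and 1.6 points, all from the sample size section. Check on the SD: 2.828 × √2 = 4.0.

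**Formula.** For a 2×2 cross-over, SE = SD/√N, noncentrality = difference/SE, and df = N − 2 = 14. Power comes from the noncentral t distribution; the critical value is 2.145.

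**The plan's own figure.** SE = 4/√16 = 1.0 and noncentrality = 3.1, so power is 82.2%. The smallest number per sequence that reaches 80% is 8, so N = 16 is reproduced. The surplus over 80% comes from rounding up. With N = 16 and SD 4, the difference detectable with 80% power is about 3.0 points.

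**Power at 1.6 points, N = 16:**

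| SD of differences | SE | Noncentrality | Power |
|---|---|---|---|
| 2 | 0.50 | 3.20 | 84% |
| 3 | 0.75 | 2.13 | 51% |
| 4 (the plan's) | 1.00 | 1.60 | 32% |
| 5 | 1.25 | 1.28 | 22% |
| 6 | 1.50 | 1.07 | 17% |

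Power of 80% at 1.6 points needs an SD of differences of about 2.1 or less. At SD 4 it needs 26 per sequence, or 52 completers. The documents give no within-patient SD for NAFLD, so the range of SDs is my assumption.

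**Level or decrease.** The first paragraph gives 1.6 ± 0.7% as the liver fat after the LGI diet. From 2.4% that is a fall of 2.4 − 1.6 = 0.8 points. The second paragraph gives the same figures as the size of the fall. At 0.8 points and SD 4, the noncentrality is 0.8 and power is about 12%.

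**What the 3.1 consists of.** On the pilot's figures the HGI diet raised liver fat by 4.7 − 2.4 = 2.3 points and the LGI diet lowered it by 0.8, which sum to 3.1. The NAFLD study gives 20.4 − 18.8 = 1.6 points within its diet-change arm over 16 weeks. It had no HGI arm.

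**Precision of a null result.** At SD 4 the 95% confidence interval has half-width 2.145 × 1.0 = 2.1 points. An interval centred on zero would include 1.6.

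**The case against.** **The NAFLD figure is a different quantity.** The 3.1 points are a contrast between two diets; the 1.6 points are a change within one arm of a study whose control was normal diet. Like for like, the patients' fall of 1.6 is twice the pilot's fall of 0.8. A provided HGI diet could widen the contrast here, and 2 weeks instead of 16 could narrow it. This stands. A reader might infer that the trial has 32% power for the effect seen in its own patient population. The documents do not support that, because they contain no estimate of the LGI-HGI contrast in NAFLD. The 1.6 is a benchmark only.

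**The SD.** A reader might infer that 4 cannot come from the pilot, since SDs of 2 and 0.7 allow at most 2 + 0.7 = 2.7. That holds only if the pilot's ± values are SDs, and the section does not label them. As standard errors with n = 7 they would imply SDs of about 5.3 and 1.9, and an SD of differences between about 3.4 and 7.1, which includes 4. The section already calls its value an assumption, and if the ± values are SDs, 4 is the cautious choice. What remains is that its source is not given.

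**What a null could exclude.** A reader might infer from the 3.0-point detectable difference that only differences of that size could be ruled out. That confuses detectability with interval width; the half-width is about 2.1 points.

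**A different SD in the second paragraph.** It might have used the 0.7 printed beside the decrease. But power at 1.6 points already exceeds 99.9% at SD 1, so 16 would not then be the number needed for 80%.

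**Disclosure.** The strengths and limitations list and the discussion concede that 2 weeks may be too short and that a small sample limits generalisability. Neither says that the power claim depends on a healthy-volunteer effect.

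**Conclusion.** The concern holds in a limited form. The calculation in the first paragraph is correct for its inputs. The claim of 80% power for a 1.6% decrease is wrong at the plan's own SD: about 32%, with 51% to 17% over SD 3 to 6. If the pilot decrease was really 0.8 points, the power for it is about 12%. The finding of sufficiency is therefore not supported by the evidence offered for it: one effect is from healthy volunteers with 2.4% liver fat, one power claim contradicts the calculation beside it, and the NAFLD study measures something else.

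The figures assume 16 completers, the cross-over analysis with 14 df and, for the main figure, SD 4. They do not show that the true contrast in NAFLD is small. It may be larger or smaller than 3.1 points, and the section should say that it is unknown.

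**What to change.** Rewrite the section as follows:

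1. State that 16 completers have 82% power for a 3.1-point contrast, the healthy-volunteer effect, and a detectable difference of about 3.0 points at 80% power, both at SD 4.
2. Give the power at 1.6 points over SD 3 to 6 (51%, 32%, 22%, 17%), labelled as a benchmark and not as the expected LGI-HGI contrast.
3. Withdraw the 80% claim for the 1.6% decrease, and settle from the pilot report whether 1.6 ± 0.7% is a level or a decrease.
4. Give the source of SD 4, and say whether the pilot's ± values are SDs or standard errors.
5. Replace the conclusion of sufficiency with a statement that the planning effect and SD are unverified in NAFLD.
6. State that a non-significant result will be interpreted through its 95% confidence interval (half-width about 2.1 points if the SD is 4), not as evidence of no effect.

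The change is wording only: no extra participants and no change to design or analysis. The cost is a less favourable stated power.
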